## 3. Death

We will describe rates of death as this is an important competing risk for outcomes. Date of death will be obtained using primary care records, which compared to the Office for National Statistics (ONS) (the gold standard), has previously been demonstrated to have 78% exact agreement and 99% agreement within 30 days. In case such accurate date coding practices have been affected by the pandemic, we will be able to link to the ONS date of death for 2020 data (we do not have access to ONS date of death linkage before 2019).

### 4.5.3 Covariates

Covariates have been determined using a directed acyclic graph (DAG) (Figure 2): demographic (age, sex), geographic region, deprivation, ethnicity, smoking, body mass index (BMI) and existing comorbidities.

For the matched historical comparison groups, we will extract covariable data as of 28 days before the index date (i.e. on the date of first recording of infection) on OpenSAFELY.

[figure not shown]

**Figure 2** Causal diagram for SARS-CoV-2 infection and end-stage renal disease

#### 4.5.3.1 Demographic

Age and sex will be included in all analyses. For descriptive purposes, we will classify age in the following categories: 18-39, 40-49, 50-59, 60-69, 70-79 and 80 years and over. In regression analyses, we will include a spline function for age to account for variation in SARS-CoV-2 infection by age.

#### 4.5.3.2 Social

It is important to account for geographical variation in SARS-CoV-2 infection rates. We will define an individual's geographical region based on NHS STP administrative regions of England grouped into East of England, London, Midlands, North East and Yorkshire, North West, South East and South West.

We will define deprivation using quintiles of IMD. IMD is assessed across seven domains of deprivation: income, employment, education, health, crime, barriers to housing and services,

and living environment. The IMD indices rank each “lower layer super output area”, derived from residential postcodes in England, from most deprived to least deprived.

We will define ethnicity using self-reported ethnicity recorded in primary care and collapsed into four high-level categories of: white, south Asian, black, and other and mixed. We expect that ethnicity will be missing for approximately 20% of our study population. For analyses adjusting for ethnicity, we will do a complete-case analysis (only including those with known ethnicity) with a follow-up sensitivity analysis.

#### **4.5.3.3 Clinical**

We will describe several clinical conditions including: cancer, cardiovascular diseases, chronic liver disease, diabetes mellitus, hypertension and immunosuppressive diseases.

We will describe baseline eGFR for each individual based on the mean eGFR recoded from 18 months to 14 days before the index date. As with follow-up eGFR, it is not possible to obtain infinite serial eGFR measurements from OpenSAFELY and so the final eGFR measurement of each calendar month before the index date (up to 18 months before the cohort start date) will be recorded for each individual. eGFR will be calculated using the CKD-EPI equation using serum creatinine measurements without adjustment for ethnicity. Baseline eGFR will be classified as follows:

1.  $\geq 105$  ml/min/1.73m^2
2. 90-104 ml/min/1.73m^2
3. 75-89 ml/min/1.73m^2
4. 60-74 ml/min/1.73m^2
5. 45-59 ml/min/1.73m^2 (CKD stage 3A)
6. 30-44 ml/min/1.73m^2 (CKD stage 3B)
7. 15-29 ml/min/1.73m^2 (CKD stage 4)
8. No eGFR measurement

We will define smoking status based on most recent primary care coding as non-smokers, ex-smokers or current smokers. We will assume that individuals with no record of smoking status are non-smokers as smoking is less common than not smoking (approximately 14% of the UK adult population were smokers in 2019). However, we will run a sensitivity analysis restricting to those with known smoking status.

BMI will be calculated using the most recent height and weight closest to the index date, then categorised as: underweight ( $<18.5\text{kg/m}^2$ ), normal weight ( $18.5\text{--}24.9\text{kg/m}^2$ ), overweight ( $25.0\text{--}29.9\text{kg/m}^2$ ), obese ( $\geq 30.0\text{kg/m}^2$ ) and undocumented (assumed to be normal in main analyses).

## 4.6 Statistical analysis

We will initially describe the baseline characteristics of people after SARS-CoV-2 infection and those from the matched historical and contemporary comparator groups.

### 4.6.1 Descriptive statistics

We will describe the baseline characteristics of people after SARS-CoV-2 infection, stratified by severity, and those from the matched historical and contemporary comparator groups.

### 4.6.2 Main analysis

Our statistical analysis plan has been informed by our DAG (**Figure 2**). The DAG has been developed based on assumptions about the causal relationship between SARS-CoV-2 infection and the study outcomes, although it may be limited by currently incomplete understanding. The DAG includes unobserved factors which may be sources of residual confounding (such as socioeconomic factors and comorbidities), as well as sources of

outcome misclassification (i.e. unobserved eGFR decline) and death post-SARS-CoV-2 infection as a competing outcome.

We will use Cox regression models to estimate cause-specific hazard ratios and 95% confidence intervals for ESRD for individuals after SARS-CoV-2 infection, stratified by hospitalisation, critical care admission, mechanical ventilation, acute KRT and AKI, compared to individuals in the i) historical and ii) contemporary comparator groups. The comparator groups have been matched on age, sex, region, socioeconomic deprivation and date.

On the basis of minimum sufficient adjustment sets from our DAG, we will run sequential regression models, i) adjusted for age, sex, socioeconomic deprivation, ethnicity, smoking and BMI and, ii) additionally adjusted for baseline eGFR, cancer, cardiovascular diseases, chronic liver disease, diabetes mellitus, hypertension and immunosuppressive diseases.

We will use robust standard errors to account for clustering by GP practice as well as on individuals as there may be overlap between those in the recorded SARS-CoV-2 infection groups and the historical comparison group (although the time periods are non-overlapping). We will assume people with missing BMI are not obese and people without a documented smoking status are non-smokers.

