### **4.6.3 Secondary analyses**

1. We will use Cox regression models to estimate cause-specific hazard ratios and 95% confidence intervals for the secondary outcomes i) 50% reduction in eGFR, ii) AKI and iii) death for individuals after SARS-CoV-2 (stratified as above) compared to individuals in the i) historical and ii) contemporary comparator groups.
2. We will undertake further Cox regression models for both primary and secondary outcomes with SARS-CoV-2 infection stratified by calendar time (i.e. February –

June 2020, July – September 2020, October – November 2020, December 2020 – February 2021, and March – January 2022) and vaccination status.

3. We will fit interaction terms to obtain cause-specific hazard ratio estimates for both primary and secondary outcomes stratified by age group, ethnicity, socioeconomic deprivation, diabetes and baseline eGFR.
4. For people who survive 28 days after hospitalisation for COVID-19, we will undertake an unmatched cohort analysis comparing kidney outcomes with a historical population followed-up from 1 February 2018 restricted to those who survived 28 days after a hospital admission for pneumonia (with or without influenza). This analysis will be stratified by critical care admission, mechanical ventilation, acute KRT and AKI, with additional adjustment for calendar month. The reason for this analysis is to investigate whether COVID-19 is responsible for long-term kidney outcomes to a greater or lesser extent than hospitalisation for other respiratory tract infections.

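### Region is a named covariate but is in neither adjustment set, so as written nothing controls for it in the unmatched COVID-19 versus pneumonia comparison

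*Protocol*

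**What the plan says.** Section 4.5.3 of the protocol says the covariates come from a directed acyclic graph and lists them: "demographic (age, sex), geographic region, deprivation, ethnicity, smoking, body mass index (BMI) and existing comorbidities". Section 4.5.3.2 gives the reason for including geography, "It is important to account for geographical variation in SARS-CoV-2 infection rates", and defines the variable: "We will define an individual's geographical region based on NHS STP administrative regions of England", grouped into seven regions.

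Section 4.6.2 sets out the models: "On the basis of minimum sufficient adjustment sets from our DAG, we will run sequential regression models". They are "adjusted for age, sex, socioeconomic deprivation, ethnicity, smoking and BMI and, ii) additionally adjusted for baseline eGFR" and comorbidities. In full, the second is "additionally adjusted for baseline eGFR, cancer, cardiovascular diseases, chronic liver disease, diabetes mellitus, hypertension and immunosuppressive diseases". The sentence closing the preceding paragraph of that section notes, for the general-population groups, "The comparator groups have been matched on age, sex, region, socioeconomic deprivation and date".

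For hospitalised patients, section 4.6.3 item 4 says "we will undertake an unmatched cohort analysis comparing kidney outcomes with a historical population" admitted with pneumonia. It describes calendar month as an additional adjustment and names no other covariate.

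**The concern.** The protocol gives two lists that should agree, the covariates from the diagram and the terms in the models, and they differ by one item. Where comparators are matched on STP, the design supplies what the model lacks. Where there is no matching, nothing does.

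The pneumonia comparison is the one meant to show whether kidney outcomes are specific to COVID-19 or follow any severe respiratory admission; sections 4.6.3 and 6 both give it that role. If infection rates varied by place, as section 4.5.3.2 says, the regional mix of COVID-19 admissions could differ from that of pneumonia admissions in earlier years. If kidney outcomes or their recording also differed by region, part of the estimated contrast would reflect geography.

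**Working it through.** The check is mainly a comparison of texts; the protocol gives no figure to reproduce.

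**Step 1: compare the lists.**

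| Covariate in 4.5.3 | Model (i), 4.6.2 | Added in model (ii), 4.6.2 | Added for pneumonia analysis, 4.6.3 item 4 |
|---|---|---|---|
| Age, sex | yes | | |
| Geographic region | no | no | no |
| Deprivation | yes | | |
| Ethnicity | yes | | |
| Smoking, BMI | yes | | |
| Comorbidities | | yes, with baseline eGFR | |
| (not in 4.5.3) calendar month | | | yes |

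Region is the only listed covariate that enters no model.

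**Step 2: ask what else could control region.**

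- *Matching.* Sections 4.4.2 and 4.4.3 match the general-population comparators on STP. The seven regions are groups of STPs, so matching on STP also matches on region. Section 4.4.2 describes the pneumonia group as unmatched.
- *Stratification by matched set.* The deviations table (row 4.6.1) reports this for the Cox models. It cannot act in an analysis without matched sets.
- *Robust standard errors by GP practice* (4.6.2). These change the variance and leave the point estimate as it is.
- *Deprivation.* IMD is a different variable and does not stand in for region.
- *Deviations table.* It keeps STP as a matching factor and moves the start of the pneumonia cohort to 1 February 2017. It adds no region term to that analysis.

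**Step 3: ask whether matching explains the omission.** Four factors other than date were matched: age, sex, region and deprivation. Model (i) still adjusts for age, sex and deprivation. The protocol therefore does not follow a rule that matched factors are left out of the model.

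**Step 4: what a bias could look like, on assumptions only.** Suppose one region supplies a share p1 of COVID-19 admissions and p0 of pneumonia admissions, and has r times the outcome rate of the rest after all other adjustment. With no true effect, the hazard ratio is shifted by about (p1·r + 1 − p1) / (p0·r + 1 − p0). Take p1 = 0.30 and p0 = 0.20; neither share nor any value of r is in the protocol.

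| r | Calculation | Shift |
|---|---|---|
| 1.1 | 1.03 / 1.02 | 1.01 |
| 1.2 | 1.06 / 1.04 | 1.02 |
| 1.5 | 1.15 / 1.10 | 1.05 |
| 2.0 | 1.30 / 1.20 | 1.08 |

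Swapping the two shares inverts each ratio: at r = 2.0 it becomes 1.20 / 1.30 = 0.92. The direction is therefore as open as the size.

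**The case against.** The best reply is that the two models in section 4.6.2 were written for the matched comparisons, where region is dealt with by design. Item 4 of section 4.6.3 gives no full covariate list, so reading it as excluding region infers something from silence, and model terms for a secondary analysis may be left to an analysis plan. Part of this stands: the protocol does not say that region will be left out. But calling calendar month an additional adjustment presupposes a base set, and the only sets stated omit region. The protocol has fixed its lists, and they disagree.

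A second reply is that a covariate drawn in a causal diagram need not belong to a minimum sufficient set, and that the reason given in section 4.5.3.2 concerns infection rates, whereas everyone in the pneumonia comparison is in hospital and exposure is separated mainly by era. This also stands in part. The figure is not available, so whether region is a necessary confounder there cannot be verified. If the diagram shows that it is not, the protocol should say so, because sections 4.5.3 and 4.5.3.2 point the other way.

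A third reply is that any bias would be small beside the hazard ratio of 1.6 in section 5. That figure is built on general-population incidence, not on a pneumonia comparator. Section 4.4.2 cites earlier work finding similar outcomes after COVID-19 and pneumonia admissions, so this ratio could lie nearer to 1. The protocol's promise of caution in section 6 concerns differences between the people who survive each illness, not geography.

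**Conclusion.** The inconsistency is real, and its consequence is confined to one secondary analysis. As written, the COVID-19 versus pneumonia comparison has no control for a covariate that the protocol itself names. This rests on reading item 4 of section 4.6.3 as the sets of section 4.6.2 plus calendar month. The size and direction of any bias are unknown, and the 1% to 8% range above is an illustration, not an estimate.

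Three stronger readings are tempting and are not supported:

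- *Region is uncontrolled throughout.* STP matching, with the matched-set stratification in the deviations table, handles it in the historical and contemporary comparisons.
- *Missing data undo the matching.* Having no eGFR measurement is a category of baseline eGFR (4.5.3.3); the exclusion for lacking one applies only to the 50% reduction outcome (4.5.2.2). Complete-case handling of ethnicity, expected to be missing for about 20%, would unbalance region only if missingness differed jointly by exposure and region. Nothing shows this, and multiple imputation is already planned as a sensitivity analysis (4.6.4). Under matched-set stratification, the comparisons that remain are still within STP.
- *Region is a proven confounder of material size.* The documents give no regional variation in kidney-failure risk or coding, and no regional distribution of pneumonia admissions.

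**What to change.** In section 4.6.3 item 4, write out the full covariate list and include the seven-level region of section 4.5.3.2, either as a covariate or as a stratum. Doing both is redundant, since a region main effect cannot be estimated within region strata. Alternatively, state why the diagram does not require region in this comparison.

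Leave matched models unchanged where they are stratified by matched set; STP is constant within a set, so a region term would do nothing. If any matched model is fitted without that stratification, add region alongside age, sex and deprivation, which model (i) already includes despite matching.

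The cost is 7 − 1 = 6 parameters as a covariate, or none as a stratum, from a variable the protocol already defines. That is negligible against the more than 200,000 hospitalised survivors expected in section 5. The deviations table says data access ended on 30 June 2024. If the pneumonia model was fitted without region and cannot be rerun, report this as a limitation of that comparison.

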### **4.6.3 Secondary analyses**

1. We will use Cox regression models to estimate cause-specific hazard ratios and 95% confidence intervals for the secondary outcomes i) 50% reduction in eGFR, ii) AKI and iii) death for individuals after SARS-CoV-2 (stratified as above) compared to individuals in the i) historical and ii) contemporary comparator groups.
2. We will undertake further Cox regression models for both primary and secondary outcomes with SARS-CoV-2 infection stratified by calendar time (i.e. February –

June 2020, July – September 2020, October – November 2020, December 2020 – February 2021, and March – January 2022) and vaccination status.

3. We will fit interaction terms to obtain cause-specific hazard ratio estimates for both primary and secondary outcomes stratified by age group, ethnicity, socioeconomic deprivation, diabetes and baseline eGFR.
4. For people who survive 28 days after hospitalisation for COVID-19, we will undertake an unmatched cohort analysis comparing kidney outcomes with a historical population followed-up from 1 February 2018 restricted to those who survived 28 days after a hospital admission for pneumonia (with or without influenza). This analysis will be stratified by critical care admission, mechanical ventilation, acute KRT and AKI, with additional adjustment for calendar month. The reason for this analysis is to investigate whether COVID-19 is responsible for long-term kidney outcomes to a greater or lesser extent than hospitalisation for other respiratory tract infections.

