## 1.2 Methods

Our study will include adults not already on dialysis and not already having received a kidney transplant. We will compare people with and without COVID-19 for differences in the rates of the following kidney complications:

1. Newly-diagnosed kidney failure (i.e. new dialysis or kidney transplant, or loss of kidney function down to less than 15% of what it should be),
2. At least 50% loss in kidney function from before they developed COVID-19,
3. Further AKI (suggesting their kidneys are more susceptible to future damage).

We will be able to determine whether outcomes vary based on the severity of COVID-19 (i.e. based on whether people required hospitalisation, intensive care, a ventilator, dialysis or had AKI), based on time (e.g. during peaks, after widespread use of effective anti-COVID-19 drugs such as steroids), and based on their levels of vaccination.

In our statistical analysis, we will account for factors such as age, sex, ethnicity, socioeconomic deprivation, smoking, BMI, and pre-existing medical problems such as diabetes.

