### 3. Objectives

Overall, our aim is to investigate long-term kidney outcomes after recorded SARS-CoV-2 infection in the general population.

Our specific objectives are:

1. To describe the relative and absolute rates of ESRD (primary outcome) after recorded SARS-CoV-2 infection compared to both contemporary and historical groups, stratified by:
  - a. Hospitalisation for COVID-19
  - b. Critical care admission for COVID-19
  - c. Mechanical ventilation for COVID-19
  - d. Acute KRT associated with COVID-19
  - e. AKI associated with COVID-19
2. To describe the relative and absolute rates of a 50% reduction in eGFR, incident AKI, and death (secondary outcomes), after recorded SARS-CoV-2 infection compared to both contemporary and historical groups, stratified by:
  - a. Hospitalisation for COVID-19
  - b. Critical care admission for COVID-19
  - c. Mechanical ventilation for COVID-19
  - d. Acute KRT associated with COVID-19
  - e. AKI associated with COVID-19
3. To describe the relative and absolute rates of these outcomes after hospitalisation for COVID-19 compared to a historical hospitalised group, stratified by:
  - a. Critical care admission for COVID-19
  - b. Mechanical ventilation for COVID-19

- c. Acute KRT associated with COVID-19
  - d. AKI associated with COVID-19
- 4. To describe the relative and absolute rates of outcomes after recorded SARS-CoV-2 infection compared to both contemporary and historical groups stratified by:
  - a. Baseline eGFR
  - b. Diabetes
  - c. Age
  - d. Sex
  - e. Ethnicity
  - f. Socioeconomic deprivation
- 5. To describe the relative and absolute rates of outcomes after recorded SARS-CoV-2 infection compared to both contemporary and historical groups additionally stratified by:
  - a. Calendar time
  - b. Vaccination status

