### 4.3 Study designs

We will compare people after SARS-CoV-2 infection to both historical and contemporary cohorts in order to address epidemiological challenges and triangulate meaningful conclusions.

Testing for SARS-CoV-2 during the early stages of the pandemic was restricted due to a lack of infrastructure; therefore many people who were infected (both symptomatic and asymptomatic) will not have been coded as such and so will be misclassified in a contemporary comparison. Using historical comparator groups will allow us to definitively ensure that the comparator group was not infected with SARS-CoV-2 during follow-up. Some comparisons will also be matched on date (i.e., to start follow-up on the same date two years before), which will allow us to account for consistent seasonal variations.

Contemporary comparator populations will account for potential biases we anticipate for any historical comparison. Using a contemporary comparator will also allow us to finely adjust for changes over time during the pandemic (with time since the start of the pandemic as the underlying timescale), such as the emergence of SARS-CoV-2 variants, changes in testing policy, changes in treatment of COVID-19, and differences in ascertainment of outcomes due to reduced access to healthcare (including blood bottle shortages in 2021).

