## 4.5 Study measures

### 4.5.1 Exposure

We will identify recorded SARS-CoV-2 infection using data from SGSS, primary care records and SUS. We will include all codes indicative of SARS-CoV-2 infection. SGSS contains the date of an individual's earliest positive SARS-CoV-2 test results from Pillar 1

(NHS and Public Health England laboratories) and Pillar 2 (commercial partners) between 1 February 2020 to the most recent available time point (i.e. the COVID-19 pandemic era).

Individuals meet criteria for inclusion in the COVID-19 exposed group if they:

- Tested positive for SARS-CoV-2 infection in SGSS
- Had a primary care code indicative of SARS-CoV-2 infection
- Discharged from hospital with an International classification of Diseases Version 10 (ICD-10) code in SUS indicative of COVID-19

The index date for those exposed to COVID-19 will be from 28 days after first recording of SARS-CoV-2 infection (i.e., after the earliest date of the record of a positive test in SGSS, primary care coding, or admission in SUS).

Looking at all identified SARS-CoV-2 infections will allow us to investigate how many adverse kidney outcomes can be prevented by preventing SARS-CoV-2 infection altogether through comparisons with people from the general population without known infection. We will also be able to investigate whether outcomes vary based on infection severity (hospitalisation, critical illness, mechanical ventilation and AKI [including requiring RRT]) as well as calendar time and vaccination status through further stratification based on morbidity coding (ICD-10 codes) from SUS. We will categorise people as i) unvaccinated if they had not received any vaccine dose at least 7 days before first recording of SARS-CoV-2 infection, ii) single dose vaccinated if they had received one vaccine dose at least 7 days before first recording of SARS-CoV-2 infection, iii) double vaccinated if they had received two vaccine doses at least 7 days before first recording of SARS-CoV-2 infection, and iv) more than double vaccinated if they had received more than two vaccine doses (including booster doses) at least 7 days before first recording of SARS-CoV-2 infection.

Hospitalised COVID-19 cases will be further investigated through a separate comparison with a historical group. Additional levels of exposure for those hospitalised will include critical care admission, mechanical ventilation, acute KRT and AKI, determined from ICD-10 and procedural codes in SUS.

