## 5. Power calculations

A study of 89,000 survivors after SARS-CoV-2 infection found increased incidence of ESRD with a hazard ratio of 2.96 (95% confidence interval 2.49-3.51).

For our power calculation, we have assumed conservatively that the effect is only found in people hospitalised with COVID-19 and that the incidence of ESRD in the general population is 0.02%. There have been over 690,000 people hospitalised for COVID-19 in England with 150,000 deaths. As OpenSAFELY-TPP comprises 40% of the population in England, after accounting for insufficient time registered with a TPP practice and missing age, sex, deprivation and ethnicity data in people hospitalised for COVID-19 based on another study, we anticipate that our sample will include over 200,000 hospitalised COVID-19 survivors for analysis. This sample size would be sufficient to detect a hazard ratio for incident ESRD >1.6 with >80% power at the 5% significance level.

| Total exposed population (SARS-CoV-2 infection survivors) | Hazard ratio for incident ESRD |      |      |      |      |      |
|-----------------------------------------------------------|--------------------------------|------|------|------|------|------|
|                                                           | 1.5                            | 1.6  | 1.7  | 1.8  | 1.9  | 2.0  |
| 100,000                                                   | 50%                            | 63%  | 74%  | 83%  | 89%  | 93%  |
| 150,000                                                   | 65%                            | 78%  | 88%  | 94%  | 97%  | 99%  |
| 200,000                                                   | 76%                            | 88%  | 94%  | 98%  | 99%  | 100% |
| 250,000                                                   | 84%                            | 93%  | 98%  | 99%  | 100% | 100% |
| 500,000                                                   | 98%                            | 100% | 100% | 100% | 100% | 100% |
| 1,000,000                                                 | 100%                           | 100% | 100% | 100% | 100% | 100% |

**Table 1** Power estimates for detecting incident ESRD in survivors of SARS-CoV-2 infection at the 5% significance level by total exposed population size, assuming an incidence of ESRD of 0.02% in the general population.

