| 4.6.2 Secondary analyses | 
A priori, we intend to fit interaction terms to obtain hazard ratio estimates stratified by age group, ethnicity, quintile of IMD, frailty group (for those aged 65 years and over only), diabetes, baseline eGFR, coded CKD, and calendar time of infection.
 
Stratified SHRs will also be reported for critical care admission, mechanical ventilation, acute RRT and AKI after COVID-19.
 
We will describe Kaplan-Meier graphs for survival after COVID-19. We will obtain p-values using log rank tests.
 | 
We fitted interaction terms for age, sex, ethnicity, diabetes, baseline eGFR, vaccination status and COVID-19 wave (i.e. calendar time of infection).
 
We obtained stratum-specific hazard ratios overall, and by hospitalization status only (i.e. hospitalised and non-hospitalised).
 
We did not produce Kaplan-Meier graphs.
 | 
We felt sex was an important potential effect modifier. We felt interaction for IMD would not provide important additional information.
 
We did not investigate interaction by frailty or coded CKD status: 1) We were unable to capture reliable time-updated measures of frailty; and 2) evidence indicates that coded CKD status does not capture CKD status as reliably as CKD stage established using serum creatinine test results to calculate eGFR measures.
 
Investigating interactions by critical care admission or acute kidney injury would have been difficult to interpret due to the high competing risk of death with our outcomes.
 
We did not have access to the data after June 30 2024 to be able to obtain standardized incidence curves as planned. We undertook assessment for
 |

|                                                                            |                                                                                                                                                                                                                                                                                                              |                                                                         |                                                                                                                                        |

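### Calendar-period hazard ratios pooled over severity mix any change in effect with a change in who is recorded as infected

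*Protocol*

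**What the plan says.** Section 4.6.3, item 2, plans this for five calendar periods and for vaccination status: "We will undertake further Cox regression models for both primary and secondary outcomes with SARS-CoV-2 infection stratified by calendar time". Item 1 of the same section carries over the severity strata of the main analysis and item 4 names its own. Item 2 does neither.

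The exposed group in section 4.5.1 is broad: "We will include all codes indicative of SARS-CoV-2 infection". A positive test, a primary care code or a hospital code each qualifies.

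On testing, section 4.3 says: "Testing for SARS-CoV-2 during the early stages of the pandemic was restricted due to a lack of infrastructure". Sections 4.3 and 6 treat this as a source of misclassified comparators. On the remedy for change over time, section 4.3 says: "Using a contemporary comparator will also allow us to finely adjust for changes over time during the pandemic". Changes in testing policy are listed among the things so adjusted, next to variants, treatment and access to care.

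The lay summary (section 1.2) says that outcomes may be compared "based on time (e.g. during peaks, after widespread use of effective anti-COVID-19 drugs such as steroids". Objective 5 in section 3 reads "compared to both contemporary and historical groups additionally stratified by", followed by calendar time and vaccination status.

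Section 5 states: "we have assumed conservatively that the effect is only found in people hospitalised with COVID-19". The deviations table (row for 4.6.2) reports that COVID-19 wave was fitted as an interaction and that stratum-specific HRs were obtained overall and "by hospitalization status only (i.e. hospitalised and non-hospitalised".

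**The concern.** Restricted testing has two consequences, and the protocol discusses one. It leaves unrecorded infections among the contemporary comparators, which sections 4.3 and 6 acknowledge. It can also select the exposed group: when tests are scarce, the infections that get recorded are likely to lean towards people ill enough to be tested or admitted. If the effect differs by severity, the HR for all recorded infection is a weighted mixture whose weights can move with testing access.

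The contemporary comparator does not remove this. Matching on date, or using pandemic time as the timescale, deals with influences that act on both arms on the same date, such as reduced access to blood tests. It cannot correct which infected people enter the exposed arm. Stratifying the Cox model by matched set, as the deviations table reports, does not correct it either, because COVID-19 severity exists only in the exposed arm.

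What is at stake is the reading of objective 5a. A fall in the pooled HR from early to late periods could be taken as a weakening effect of COVID-19 on the kidney, and the example in the lay summary invites a link to treatment. The same fall could arise with no change in effect within either severity group.

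**Working it through.** **The plan's own figure.** The protocol gives no figure for case mix. The nearest calculation is Table 1, which rests on the assumption that the effect lies in hospitalised cases. For 200,000 exposed, five comparators each, risk 0.02% and HR 1.6:

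- Expected events: 200,000 × 0.00032 = 64 exposed; 1,000,000 × 0.0002 = 200 comparators. Pooled risk = 264 / 1,200,000 = 0.00022.
- Standard error under the null: √[0.00022 × (1/200,000 + 1/1,000,000)] = 0.0000363. Under the alternative: √[0.00032/200,000 + 0.0002/1,000,000] = 0.0000424.
- z = (0.00012 − 1.96 × 0.0000363) / 0.0000424 = 1.15, so power is 87.5% (stated 88%).

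All 36 cells of Table 1 reproduce to within 1 percentage point. The table is sound on its assumptions, but it concerns power, not case mix.

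**Inputs for the illustration.**

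- HR in non-hospitalised cases = 1: the section 5 assumption. The deviations table (row for 4.3) also reports no effect in that group.
- HR in hospitalised cases, constant over time: assumed. I use 3 and 2, then 2.96 (the all-survivor HR cited in section 5, borrowed for illustration) and 1.6 (the detectable HR in section 5).
- w, the hospitalised share of recorded cases in a period: not in the documents, so a range is assumed.
- b, the baseline risk of hospitalised relative to other cases: assumed 1, then 2.

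**Formula** (rare outcome): pooled HR = [w × b × HR_hosp + (1 − w)] / [w × b + (1 − w)]. With b = 1 this is w × HR_hosp + (1 − w).

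**Results with b = 1.**

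- HR_hosp = 3: 0.50 × 3 + 0.50 = 2.0; 0.05 × 3 + 0.95 = 1.1.
- HR_hosp = 2: 0.50 × 2 + 0.50 = 1.5; 0.05 × 2 + 0.95 = 1.05.

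| w | HR_hosp 2.96 | HR_hosp 1.6 |
|---|---|---|
| 60% | 2.18 | 1.36 |
| 40% | 1.78 | 1.24 |
| 20% | 1.39 | 1.12 |
| 10% | 1.20 | 1.06 |
| 5% | 1.10 | 1.03 |

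**Results with b = 2 and HR_hosp = 2.96.**

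- w = 60%: (1.2 × 2.96 + 0.4) / 1.6 = 2.47.
- w = 5%: (0.1 × 2.96 + 0.95) / 1.05 = 1.19.

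In every row the severity-specific HRs are held fixed, so the whole movement in the pooled HR comes from w.

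**The case against.** The strongest reply has four parts.

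1. **The crossing was done.** The deviations table reports HRs for wave by hospitalisation status as well as overall. This stands, and it narrows the practical gap: a reader of the results can set the two side by side. It leaves item 2 and section 4.3 as they are, and the overall HRs by wave were still produced.

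2. **Item 2 may already mean crossed.** Objective 5 speaks of additional stratification, and section 4.5.1 mentions calendar time together with severity. The wording is open to that reading. Item 1 repeats the severity strata explicitly and item 2 does not, so the text needs settling.

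3. **The objective is descriptive.** No section plans to attribute a difference between periods to treatment, variants or vaccination. That is correct. The risk lies in how the trend would be read, given the example in the lay summary.

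4. **Severity follows infection.** If vaccines, variants or treatment act by changing who becomes severely ill, analysing only within severity removes part of a real change. The all-infection estimate also has its own purpose in section 4.5.1: the kidney outcomes avoidable by preventing infection altogether. Section 2.1 notes that admission criteria vary between settings, so the hospitalised group is itself selected. This stands, and it rules out replacing the pooled HR with the hospitalised HR as the sole answer to objective 5a.

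A reader might also infer that the pooled trend shows only the changing share of severe cases and says nothing about a changing effect. The documents do not support that. They give no hospitalised share for any period, they admit exposure through primary care and hospital codes as well as tests, and variants, treatment and vaccination changed over the same months.

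**Conclusion.** The concern holds as one of interpretation. As written, item 2 yields calendar-period HRs pooled over severity. Their trend combines any change in effect with any change in who is recorded, and those figures alone cannot separate the two. Two of the protocol's own statements carry the argument: early testing was restricted, and the effect is assumed to lie in hospitalised cases.

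The size is unknown. The illustrations show that a wide shift in the hospitalised share could by itself move the pooled HR from 2.0 to 1.1, or only from 1.36 to 1.03 if the hospitalised HR is 1.6 and the share falls from 60% to 5%. They show what is possible, not what is likely, and rest on assumed shares, constant severity-specific HRs and the stated baseline risks.

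The statement in section 4.3 that a contemporary comparator adjusts for changes in testing policy is too broad: it cannot hold for selection into the exposed arm. This affects a secondary analysis and leaves the severity-stratified main analysis untouched. It is worth correcting because the correction is cheap and a pooled trend is easily misread.

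**What to change.** - **Section 4.6.3, item 2:** state that calendar-period HRs are also estimated within hospitalised and within non-hospitalised COVID-19, in line with what the deviations table reports.
- **Pooled HR by period:** keep it as descriptive, print the hospitalised share of recorded cases in each period beside it, and say that its trend is not read as a change in effect.
- **Limitation to add:** admission thresholds may also drift over time, and severity may mediate part of a real change, so neither stratum is free of selection.
- **Section 4.3:** remove changes in testing policy from the factors that the contemporary comparator is said to adjust for, or limit the claim to influences acting on both arms on the same date.

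The cost is mainly wording, since the deviations table indicates that the crossed estimates exist; the hospitalised share per period is a simple tabulation. The downside is fewer events per cell and wider intervals, most of all in the smaller periods.
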